#### Sample size

2.2.3

For the behavioral assessment using the CRS-R, this study adopts a randomized controlled intervention design. Repeated measures will be analyzed using ANOVA to account for potential confounding variables. Based on a power analysis conducted using G*Power, with an effect size of 0.40, a significance level (*α*) of 0.05, statistical power (1 − *β*) of 0.80, a two-tailed test (α = 0.05), and an equal allocation ratio among the three groups (N1: N2: N3 = 1:1:1), the required each group sample size is calculated to be 18. After applying Bonferroni correction, the significance threshold for individual comparisons should be adjusted to α = 0.0167. To maintain this corrected alpha level, each group would require a sample size of 22. Considering a potential 15% dropout or exclusion rate, a minimum of 76 participants is required. Therefore, the study will enroll a total of 78 participants: 26 in Group A, 26 in Group B, and 26 in Group C. In the event of patient withdrawal or death during the study, we will implement standardized procedures. All withdrawal cases will be documented systematically, including: (1) voluntary withdrawal (participant-initiated consent revocation), (2) loss to follow-up (≥3 consecutive contact attempts failed), (3) clinical deterioration (≥2-point GCS decrease sustained for 48 h), and (4) investigator-determined withdrawal (with protocol-specified justification). For data management, all collected pre-withdrawal data will be retained per intention-to-treat principles, with final evaluable assessments carried forward for primary analysis. Mortality cases will trigger immediate reporting to the Ethics Committee of Shanghai Yangzhi Rehabilitation Hospital (Shanghai Sunshine Rehabilitation Center), followed by survival analysis using Kaplan–Meier methodology and independent adjudication of causes by a clinical endpoint committee. Statistical approaches will include sensitivity analyses (completers vs. non-completers) and multiple imputation for missing data.

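### The comparison labelled as the missing-data sensitivity analysis (completers against non-completers) is a poor check on a carried-forward primary analysis, and the multiple imputation named beside it has no stated role

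*Protocol article*

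**What the plan says.** Everything on this point stands in one paragraph of the protocol, section 2.2.3 (Sample size).

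- **Primary handling.** Data collected before withdrawal are kept under an intention-to-treat label, "with final evaluable assessments carried forward for primary analysis".
- **Sensitivity analysis and imputation.** "Statistical approaches will include sensitivity analyses (completers vs. non-completers) and multiple imputation for missing data". The comparison in parentheses is the only item labelled a sensitivity analysis. The text does not say whether multiple imputation replaces, supplements or checks the carried-forward analysis.
- **Who is a non-completer.** Four withdrawal reasons are listed. One is neurological decline: "3) clinical deterioration (≥2-point GCS decrease sustained for 48 h". The other three are revoked consent, repeated failure to reach the patient, and a decision by the investigator. Deaths are treated separately, "followed by survival analysis using Kaplan–Meier methodology and independent adjudication of causes by a clinical endpoint committee".
- **Expected loss.** 15% for dropout or exclusion, with 26 patients per arm and 78 in all.

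**The concern.** A sensitivity analysis for missing data should re-estimate the treatment contrast under another assumption about the outcomes that were not seen, and show whether the conclusion changes. The labelled comparison does this poorly on either reading.

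*Literal reading.* Patients who finished are compared with patients who did not. This describes who left. It leaves the contrasts among the three arms untouched.

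*Completers-only reading.* The arms are compared among those who finished. Finishing is determined after randomisation, and one defined way of not finishing is neurological decline. If one arm has more such withdrawals, its remaining patients look better than the arm as randomised.

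Carry-forward has a related weakness: for a patient withdrawn after declining, the last evaluable score may predate the decline. The check and the primary analysis can then lean the same way, and their agreement would be read as robustness.

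**Working it through.** **1. The plan's own figures.** 22 per group × 3 = 66. Then 66 × 1.15 = 75.9, which gives the stated minimum of 76. Dividing instead, 66 / 0.85 = 77.6, gives 78, the number enrolled, so there is no shortfall. The 15% loss is 0.15 × 78 = 11.7, about 12 patients, or 0.15 × 26 = 3.9, about 4 per arm.

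**2. Bias of a completers-only mean.** Let a fraction p of an arm be lost, and let those patients' unseen outcomes lie δ below the completers' mean M. The mean of the whole arm is (1 − p)M + p(M − δ) = M − pδ, so completers overstate the arm by pδ. With p = 0.15 from the plan and δ assumed:

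- δ = 0.5 SD: 0.075 SD
- δ = 1 SD: 0.15 SD
- δ = 1.5 SD: 0.225 SD

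For a contrast of two arms the bias is p₁δ₁ − p₂δ₂. It is zero when rate and kind of loss match. With δ = 1 SD in both arms and losses of 23% and 8%, it is 0.23 − 0.08 = 0.15 SD.

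**3. Scale.** The plan assumes a difference "with an effect size of 0.40" without naming the measure. Read as Cohen's f (an assumption), it implies a largest pairwise difference of 0.40 × 3/√2 = 0.85 SD if one arm differs from two equal arms, or 0.40 × √6 = 0.98 SD if the arms are equally spaced. A bias of 0.15 SD is then 15% to 18% of the planned difference (0.15/0.98 to 0.15/0.85). The standard error of a two-arm contrast at 22 per arm is √(2/22) = 0.30 SD, so the bias is half a standard error.

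**4. Can the check and the primary analysis err together?** Simulation of 3,000 trials per row. All settings are assumptions: two arms of 26, baseline–outcome correlation 0.7, the patients with the worst change are the ones lost, and carry-forward means no change from baseline. Estimates are in baseline SD units.

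| True effect | Loss, active / sham | Completers only | Carry-forward |
|---|---|---|---|
| 0 | 15% / 15% | 0.00 | 0.00 |
| 0 | 23% / 8% | +0.18 | +0.12 |
| 0 | 8% / 23% | −0.18 | −0.12 |
| 0.80 | 15% / 15% | 0.80 | 0.68 |
| 0.80 | 23% / 8% | 0.98 | 0.74 |
| 0.80 | 8% / 23% | 0.62 | 0.62 |

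With no true effect and unequal loss, both methods err in the same direction. The last row shows the same with a true effect: they agree and are both too low. In the fifth row they lie on opposite sides of the truth, so shared bias is possible, not certain. Making every lost patient one of the worst changers is severe, since deterioration is only one of four withdrawal reasons.

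**5. The literal reading.** No arm contrast is computed, so there is no bias to quantify. The comparison is also coarse: for about 12 against 66 patients the standard error is √(1/12 + 1/66) = 0.31 SD.

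**The case against.** The strongest reply is that the same sentence names multiple imputation. That method re-estimates the arm effect in all randomised patients under an assumption different from carry-forward, so setting the two side by side is a real check. The wording also leaves the list open. This stands. A reader might infer that the plan has no means of showing whether its result survives missing data; the document does not support that. What remains is that imputation has no stated role and, in its standard form, assumes missing at random, which is doubtful when deterioration is a withdrawal reason.

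Three further limits stand.

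- A reader might infer that a completers-only analysis removes just the patients who deteriorated. It does not: there are three other withdrawal reasons, deaths also end follow-up, and nothing suggests that deterioration predominates.
- A reader might infer that non-completers have no outcome. Sections 2.3 and 2.4.1 place CRS-R assessments around each of two sessions 2 to 3 days apart and average the scores over sessions. Many later withdrawals will therefore have post-treatment scores, and a comparison by completion status is feasible and informative as description. Missingness in that averaged score may be well below 15%, and more will fall at 1, 3 and 6 months.
- A reader might infer that the method always favours a harmful arm. It does so only if loss differs by arm in rate or kind. Harm could also show in documented withdrawals, adjudicated deaths and the adverse-event tests of section 2.5.

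It can also be said that a tipping-point analysis belongs in the statistical analysis plan, which is not shown. Its absence alone would indeed be no finding. But the protocol does more than stay silent: it states what its sensitivity analysis is, and that choice is a poor one.

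**Conclusion.** The point holds in a limited form and is minor. The labelled sensitivity analysis either does not re-estimate the arm contrasts or conditions on a post-randomisation event that includes deterioration. None of the three named approaches (carry-forward, the completer comparison, standard multiple imputation) tests outcome-dependent loss that differs by arm.

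The illustrative size is 0.15 SD, about half a standard error of a two-arm contrast. It rests on 15% loss in one arm, unseen outcomes 1 SD lower there, and no offsetting loss in the comparator. The 1 SD is assumed and scales the result directly. With loss alike across arms the bias roughly cancels, but whether the unseen outcomes are alike cannot be verified from the observed data.

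**What to change.** In section 2.2.3, replace the parenthetical comparison of completers with non-completers by: *the arm contrasts re-estimated in all randomised patients under multiple imputation, first under missing at random and then with imputed values of withdrawn patients shifted downward by arm (delta-adjusted), reporting the shift at which the conclusion changes.* This also gives the imputation a defined role. Keep the comparison of completers and non-completers, by arm, as description only. The withdrawal criteria and the separate handling of deaths are not affected.

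The cost is one sentence and a few extra runs of an imputation already planned. No additional data or patients are needed.

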#### Randomization

2.2.4

Randomization will be performed using the random number generation function in the R programming language (set.seed). All eligible participants will be randomly assigned to one of three groups in a 1:1:1 ratio: Group A (100 Hz TUS), Group B (tbTUS), and Group C (sham stimulation). To ensure allocation concealment and fairness, a randomization sequence will be generated by an independent researcher who is not involved in the trial’s implementation or outcome evaluation. The randomization sequence will be kept confidential and will not be disclosed to outcome assessors or statisticians. Baseline assessments will be completed after group assignment. Healthcare providers and therapists involved in the participants’ care, including acupuncturists and cognitive therapists, will remain blinded to group allocation to minimize bias.

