
Currently, despite a growing landscape of studies investigating non-invasive neuromodulatory treatments for pDoC (12, 13), none has yet been established to systematically improve consciousness levels or functional recovery in this population. First, regarding transcranial direct current stimulation (tDCS) (14), a multicenter randomized clinical trial conducted in 2023 evaluated the effects of tDCS during rehabilitation. While no significant therapeutic effect was observed at the group level, subgroup analysis at a 3-month follow-up revealed notable improvements in patients with minimally conscious state (MCS) and traumatic etiologies. Second, in the field of transcranial magnetic stimulation (TMS) (15), repetitive TMS (rTMS) applied to the dorsolateral prefrontal cortex in 16 patients with DoC (5 MCS and 11 VS/UWS) resulted in increased (the Coma Recovery Scale-Revised) CRS-R scores in 36% of VS/UWS patients and all MCS patients. Moreover, a 2022 study applying 20 Hz rTMS (16) demonstrated significant improvements in consciousness in the real stimulation group compared to the sham group. However, in-depth analysis revealed that only a subset of patients experienced clinically meaningful gains. Third, for transcutaneous auricular vagus nerve stimulation (taVNS), a 2023 randomized double-blind controlled trial (17) involving 57 DoC patients found that while the intervention group showed higher CRS-R scores post-treatment compared to the control group, the difference did not reach statistical significance. Finally, in the realm of Low-intensity focused ultrasound pulses (LIFUP), Monti et al. (18) pioneered the use of non-invasive ultrasound to stimulate the thalamus (100 Hz TUS) in a patient with MCS following traumatic brain injury in 2016. The patient exhibited significant clinical improvement, marking a pivotal moment in the application of LIFUP for DoC. Subsequent studies have reported increases in CRS-R scores in both acute (19) and chronic (20) DoC cases. However, The absence of rigorous comparison with a sham stimulation group limits these findings, highlighting the need for controlled investigations.

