### Interventional methods

2.3

After initial screening and evaluations, all patients in the three groups will undergo two sessions of LIFUP. Prior to LIFUP, K-Plan simulation will be performed to determine the optimal stimulation trajectory. Prior to the intervention, baseline assessments will be conducted within a 7- to 10-day window, including five repeated CRS-R evaluations, HD-EEG, SSEPs, fMRI, MRS and PET-CT. The first session of LIFUP will be administered between days 11 and 13, with the second session delivered after a 2- to 3-day interval. Each stimulation session will be conducted according to its corresponding parameter specific duration. CRS-R evaluations will be conducted 1 h before and after each session of LIFUP. Following the second session of LIFUP, repeat assessments including EEG, SSEPs, fMRI, MRS, and PET-CT will be conducted, with all evaluations completed within 5–7 days post-intervention. The intervention phase will last approximately 23 days in total. The entire process of examination and treatment is shown in Figure 2.

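### Baseline is completed after group assignment, so patients can be lost after randomisation but before any treatment

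*Protocol article*

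**What the plan says.** **Order.** The Randomization section (2.2.4) states "Baseline assessments will be completed after group assignment".

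**Length and content of baseline.** Under Interventional methods (2.3), "baseline assessments will be conducted within a 7- to 10-day window, including five repeated CRS-R evaluations, HD-EEG, SSEPs, fMRI, MRS and PET-CT". K-Plan simulation must also precede stimulation. Then, "The first session of LIFUP will be administered between days 11 and 13".

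**Eligibility.** A CRS-R profile of VS/UWS or MCS and a stable past week are required at entry (2.2.1). The article does not say that stability is checked again before session 1.

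**Arm sizes and losses.** Sample size (2.2.3) says "the study will enroll a total of 78 participants: 26 in Group A, 26 in Group B, and 26 in Group C". It allows 15% for dropout or exclusion, keeps data collected before withdrawal under intention-to-treat, carries the last evaluable assessment forward for the primary analysis, and also names multiple imputation and a completer versus non-completer sensitivity analysis.

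**Blinding.** The sequence is made by an independent researcher and withheld from outcome assessors and statisticians; care staff and therapists are blinded (2.2.4). Those who plan targets or operate the transducer are not mentioned. Sham is given with the transducer's power supply off (2.3.1).

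**The concern.** The order creates an avoidable gap between randomisation and treatment in an unstable population. The article's own list of common causes of instability (fever, seizures, sympathetic hyperactivity, poor oxygenation) describes events that can recur within two weeks. Unsuitability can also emerge late: the Target section (2.3.3) advises against stimulation in patients with large skull defects, yet the exclusion list (2.2.2) does not name them, so such a patient could be randomised and then not treated. Those two sections need to be reconciled in any case.

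Three things are at stake:

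- Losses before treatment draw on the same 15% allowance that is meant to cover losses during treatment and six months of follow-up.
- A patient lost after baseline but before session 1 has the baseline score carried forward, so enters the primary analysis with zero change and no treatment.
- Withdrawal at the investigator's discretion is permitted. If someone who knows the arm influences it, loss could differ between arms, and no analysis fully repairs that.

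The reference CRS-R in the pre/post comparison is likewise taken after assignment, so its integrity depends on masking and not on timing.

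**Working it through.** **1. The timeline.** Taking the upper ends in section 2.3: session 1 by day 13, session 2 up to 3 days later, repeat assessments up to 7 days after that. 13 + 3 + 7 = 23, which reproduces the article's approximate 23-day total. The day count therefore appears to start with the baseline window. The article does not tie assignment to any day of it. If assignment is on day 1, the gap to treatment is up to about 13 days. If part of baseline precedes assignment, it is shorter.

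**2. The allowance.** The stated requirement is 22 per arm, so 3 × 22 = 66.

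- 66 × 1.15 = 75.9, rounded up to 76, the stated minimum.
- 66 / (1 − 0.15) = 77.6, rounded up to 78, the number to be enrolled.

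The reserve is 78 − 66 = 12 patients, or 4 per arm.

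**3. Loss before session 1.** The rate *d* is not given, so it is assumed:

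| *d* | lost of 78 (78*d*) | left per arm, 26(1 − *d*) |
|---|---|---|
| 5% | 3.9 | 24.7 |
| 10% | 7.8 | 23.4 |
| 15% | 11.7 | 22.1 |

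At 15% the reserve of 12 is gone before anyone is treated.

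**4. Effect of carry-forward.** If a fraction *d* of each arm is lost after baseline and enters with zero change, an arm's mean change becomes (1 − *d*)μ + *d* × 0. The difference between two arms is then (1 − *d*)(μ₁ − μ₂), which is 0.95, 0.90 or 0.85 of the true difference for the three rates above. This assumes equal loss in all arms. With unequal loss the contrast is distorted in a direction that cannot be predicted.

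**5. A case that the rule may not cover.** A patient lost before any baseline CRS-R has only the eligibility CRS-R. The article does not say whether that score counts as evaluable.

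**6. Secondary point: MCS share.** The Introduction reports that in a tDCS trial "subgroup analysis at a 3-month follow-up revealed notable improvements in patients with minimally conscious state (MCS) and traumatic etiologies", and that CRS-R rose after rTMS in 36% of VS/UWS patients and in all MCS patients. Suppose the arms are fixed at 26 and the list is not stratified. The numbers of MCS patients in the arms are then multivariate hypergeometric. With *M* MCS patients among 78,

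P(*a*, *b*, *c*) = C(26, *a*) C(26, *b*) C(26, *c*) / C(78, *M*), with *a* + *b* + *c* = *M*.

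A gap of 20 points in 26 patients is 5.2, so at least 6 patients. Summing over all splits whose largest and smallest counts differ by 6 or more:

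| assumed MCS prevalence | *M* | some pair of arms differs by ≥ 20 points | one given pair |
|---|---|---|---|
| 30% or 70% | 23 or 55 | 22% | 9.5% |
| 40% or 60% | 31 or 47 | 27% | 12% |
| 50% | 39 | 27% | 13% |

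**The case against.** **Losses are partly provided for.** The 15% covers exclusion as well as dropout, data collected before withdrawal are kept, and imputation and a sensitivity analysis are named. Intracranial metal and MRI-unsafe infection are screened at entry, cranial CT is already available, and every randomised patient should have at least the eligibility CRS-R. All of this stands. It limits the damage, but it does not prevent the loss or restore the power spent on untreated patients.

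**Differential loss is hypothetical.** No stimulation has been given in this period, so loss cannot be a treatment effect, and assessors and care staff are masked. A masked baseline taken before treatment is not biased merely because it follows assignment. This also stands. What remains open is knowledge of the arm by those who plan or deliver stimulation, on which the article is silent.

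**Completed may not mean begun.** Baseline may start before assignment and only finish afterwards. That shortens the interval but leaves part of baseline after randomisation.

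**Stronger readings that the article does not support.**

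- A reader might infer simple, unrestricted randomisation, because section 2.2.4 names only R's random number generator, and so doubt the 26/26/26 split. The article does not say this. A shuffled list of 78 fits both the generator and the fixed arm sizes, and a condensed article commonly leaves blocks and strata to the full protocol.
- A reader might blame late baseline for imbalance in VS/UWS versus MCS. That status is known at eligibility, before assignment, so timing does not cause it.
- A reader might treat the day 11 to 13 session as setting a minimum gap. It does not, since assignment is not tied to day 1.

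**Conclusion.** The point holds for the order of events, which the article states outright. Patients can be lost between randomisation and first treatment, over up to about 13 days if assignment is on day 1, and the baseline CRS-R in the primary comparison is measured after randomisation. The loss is about 4 to 12 of 78 at assumed rates of 5% to 15%; the true rate is unknown. With equal loss the expected harm is dilution and lost power. Bias needs arm-dependent loss, which is possible but not shown. Nothing in the article requires this order, because treatment waits for baseline in any case.

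Stratification is a lesser matter and no error in the article. The 22% to 27% chance of a 20-point gap in MCS share rests on an assumed prevalence of 30% to 70%, fixed arms of 26, no stratification and a threshold chosen for illustration. It is chance imbalance and not systematic bias.

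**What to change.** Replace the sentence in section 2.2.4 with: *Allocation is released only after all baseline assessments and k-Plan planning are complete, immediately before session 1.* The description of the simulation does not make the choice of target depend on the arm, so planning can be done before release.

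The cost is that the independent researcher releases each allocation later. No assessment is added and the target stays at 78, now counted as patients randomised. Patients who fall out during baseline are then never randomised. If they are replaced, a few more people go through baseline than are allocated.

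Optional: stratify the list by VS/UWS versus MCS at eligibility, and include that status as a factor in the primary model. If permuted blocks are used within strata, incomplete final blocks can move the arms slightly away from 26 each, and the protocol should accept that.

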### Interventional methods

2.3

After initial screening and evaluations, all patients in the three groups will undergo two sessions of LIFUP. Prior to LIFUP, K-Plan simulation will be performed to determine the optimal stimulation trajectory. Prior to the intervention, baseline assessments will be conducted within a 7- to 10-day window, including five repeated CRS-R evaluations, HD-EEG, SSEPs, fMRI, MRS and PET-CT. The first session of LIFUP will be administered between days 11 and 13, with the second session delivered after a 2- to 3-day interval. Each stimulation session will be conducted according to its corresponding parameter specific duration. CRS-R evaluations will be conducted 1 h before and after each session of LIFUP. Following the second session of LIFUP, repeat assessments including EEG, SSEPs, fMRI, MRS, and PET-CT will be conducted, with all evaluations completed within 5–7 days post-intervention. The intervention phase will last approximately 23 days in total. The entire process of examination and treatment is shown in Figure 2.

